| We hypothesize that the use of a human coach-supported digital/AI personal health assistant (app) will improve adherence to cholesterol-lowering medications (statins with or without ezetimibe) among patients with hyperlipidaemia and suboptimal LDL-C control, when compared to standard care. |
| - 1. **Primary Objectives** |
| To evaluate the effectiveness of the human coach-supported digital/AI personal health assistant (intervention) on adherence to lipid-lowering medication at 6 and 12 months compared with those receiving standard care. |
| - 1. **Secondary Objectives**  1. To evaluate the impact of human coach-supported digital/AI personal health assistant on blood LDL-cholesterol levels at 6 and 12 months compared with those receiving standard care. 2. To evaluate the impact of human coach-supported digital/AI personal health assistant on atherosclerotic cardiovascular disease (ASCVD) risk at 6 and 12 months. 3. To evaluate the impact of human coach-supported digital/AI personal health assistant on health motivation and attitudes, self-care efficacy, self-care behaviours, and quality of life at 6 and 12 months. 4. To evaluate the acceptability of a new model of care 5. To evaluate the safety of a new model of care 6. To evaluate the (cost) effectiveness of human coach-supported digital/AI personal health assistant (intervention) on adherence to lipid-lowering medication at 12 months compared with those receiving standard care. |
| - 1. **Potential Risks and benefits:** |
| Potential Risks |
| There is minimal risk of loss of privacy breach associated with the use of mobile app. For example, if there is a data breach, someone who is not authorised could get information collected in the app. This chance is small, but it is not zero. There will be measures in place to minimum the risks in this study. |
| Potential Benefits |
| Patients in the intervention group will get full access the app and personalized Health Coaching sessions with a trained personnel to optimize management of their health condition for 12 months. |
| 1. **STUDY POPULATION** |
| List the number of patients to be enrolled. |

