| 1. **Clinical data:** Clinical data will be collected on a patient’s demographic details, past medical history, medication use, blood test results and anthropometric measurements. 2. **Questionnaires**: Onboarding questionnaire, DOSE Non-Adherence Measure and Psychometric Battery Questionnaires will be administered by the CRC 3. **Pill count**: Patients are required to bring along their prescribed lipid-lowering medications during their follow-up visits (@3m, 6m, and 12m). CRC will carry out pill counts with the patients during the visits. 4. **Medical care follow-up**: Standard-of-Care clinical pharmacist will follow-up with patients, titrating lipid-lowering medication (such as statin, ezetimibe etc) as required, and review and take action clinical blood test results (Appendix B; e.g lipid level, blood creatinine kinase and liver function tests where relevant). 5. **Human-AI-health coaching (For intervention only):** Health coach will use the information gathered by the AI chatbot to guide the targeted behavioural intervention during phone consultation. The scope of coaching will be strictly related to the medication adherence and general well-being. The coach will not start, stop, or titrate any medication. Coach will escalate concerns to clinical pharmacists when deemed fit. 6. **Focus group discussion (sub-study):** This will be conducted with a nested sample of 30-50 intervention group patients. The aims are: (a) to collect insights from intervention patients on their experiences with the app and human health coaching, (b) insights into which intervention components work best for them and under what circumstances, (c) insights into concerns which might impact intervention effectiveness, (d) factors that draw their participation and sustained engagement, (e) factors that deter them from sustainable engagement, (f) factors that may lead other CVD patients to be more inclined to partake in such a intervention and (g) ideas and suggestions to make the intervention more appealing and effective. |
|  |
| Randomisation and Blinding |

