| It is important to store the data securely and used in a way its integrity is not compromised. Data obtained from the app will be stored on a local secured cloud platform and only accessible to authorised study team members (PI, co-Is, CRCs, pharmacists). Clinical data will be stored in a secure database, accessible only to the PI, co-Is, CRCs, pharmacists. The use of the data from the study will be controlled by the PI. |
| **SAMPLE SIZE AND STATISTICAL METHODS** |
| Determination of Sample Size |
| A total of 376 patients (188 per arm) are to be recruited. The computation takes into account a) 5 level of significance, b) desired statistical power of at least 90%, c) the potential application of a mixed-effect model in view of the multi-centre design, and to cater for the random effects of repeated measurements, d) a small effect size to be detected (i.e., <0.2), e) fewer than 10 predictors to be accommodated in model building and f) no more than 20% drop outs. A post-hoc power calculation should be facilitated after the data analysis is performed. |
| Statistical and Analytical Plans |

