| The data collected will be screened for accuracy, missing data, outliers, and statistical assumptions. Following the principles of intention-to-treat (ITT) analysis, individuals will be retained in the group they were randomized to. At each measurement time, efforts will be made to minimize missing outcome data, and the reasons for individuals' loss of follow-up will be recorded. Missing data will be imputed using averages of answered items with no more than 20% missing data. When more than 20% of the items are missing, the overall score is not computed, and the data is considered missing. Sensitivity analyses will also be performed to determine the robustness of the assumption about missing data.  Descriptive statistics of baseline and follow-up data will be reported by mean and standard deviation for normally distributed variables, median and interquartile range for non-normally distributed variables, and proportions (count and percentage) for categorical variables. Continuous variables that are not normally distributed will be approximately normalised by using transformations and categorisations whenever applicable. Between group comparisons (by gender, age group, years since diagnosis, etc) will be made using Pearson χ2 or Fisher's exact test for categorical data, whereas continuous data will be tested with independent t-test and Mann–Whitney U test to evaluate changes between baseline and end-of-trial measures.  This study will also include regression/ modelling analyses to adjust potential confounders in this study such as gender, disease duration, number of comorbidities, and hypercholesterolemia treatment modalities (statins only, or ezetimibe, or statins plus ezetimibe). Subgroup analysis may be performed if the potential confounders found to be significant.  STATA (StataCorp Statistics for Windows, Version X, College Station, Texas) and R version X (The R Foundation for Statistical Computing; Vienna, Austria) will be used for all statistical analysis. All statistical tests will be performed using two-sided tests at the 0.05 significance level. |

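### Two unranked primary time points, no named primary adherence measure and 0.05 for every test leave the primary claim without a guaranteed 5% error rate

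*Protocol*

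**What the plan says.** - **Primary Objectives (section 2).** There is one primary objective, on two occasions: "To evaluate the effectiveness of the human coach-supported digital/AI personal health assistant (intervention) on adherence to lipid-lowering medication at 6 and 12 months", compared with standard care. No instrument is named and neither occasion is put first.
- **Methods and Assessments (section 6) and Table 1.** Two adherence measures are collected. For one, "CRC will carry out pill counts with the patients during the visits" (3, 6 and 12 months). For the other, "Onboarding questionnaire, DOSE Non-Adherence Measure and Psychometric Battery Questionnaires will be administered by the CRC"; Table 1 schedules DOSE at 0, 3, 6 and 12 months. Neither is called primary anywhere.
- **Section 10.1.** On the sample size: "The computation takes into account a) 5 level of significance". The inputs also include "the potential application of a mixed-effect model in view of the multi-centre design". No outcome or time point is attached to the 376 patients.
- **Section 10.2.** "All statistical tests will be performed using two-sided tests at the 0.05 significance level". The simple between-group tests are there "to evaluate changes between baseline and end-of-trial measures". No order of testing, adjustment or rule for success is given.

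**The concern.** The primary variable and its time point fix what the 5% level refers to. Here the protocol gives two occasions, leaves the measure open, and applies 0.05 to each test. Someone following the text could report a significant result at 6 months or at 12 months, on either measure, as meeting the primary objective. The error rate of that claim would then exceed the 5% used for the sample size.

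Interpretation is also at stake. DOSE is a questionnaire and pill count is a physical count. The trial is open-label, and the coordinators who carry out both learn the allocation. The two measures may disagree, and so may 6 and 12 months. The protocol then has no defined primary answer, and the deciding result could be chosen after the data are seen.

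**Working it through.** **Plan's own figure.** The protocol states no overall error rate for the primary claim. Its only related figure is 376 patients at 5% significance and at least 90% power, for an effect below 0.2 with up to 20% dropout. That figure can be neither reproduced nor refuted, because the effect-size metric, outcome and time point are not stated.
- Read as a standardised mean difference of 0.2: n per arm = 2(1.960 + 1.282)² / 0.2² ≈ 526, so 1052 in total and 1052 / 0.8 = 1315 after dropout.
- By contrast, 188 per arm matches 150 / 0.8 = 187.5, rounded up. For 90% power, 150 per arm needs a difference of about 0.374.

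**Inputs for the error rate.** From the protocol: two time points, two collected measures, two-sided 0.05 per test. Not in the protocol, so assumed: the correlation between results at 6 and 12 months, and between DOSE and pill count.

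**Case A: one measure, success at either time.**
- Bound (independent tests): 1 − 0.95² = 9.75%. For jointly normal two-sided tests, correlation only lowers this.
- With correlation, P(|Z₁| > 1.96 or |Z₂| > 1.96):

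| Correlation between times | Either direction | False claim of benefit only |
|---|---|---|
| 0.5 | 9.1% | 4.5% |
| 0.6 | 8.8% | 4.4% |
| 0.7 | 8.3% | 4.2% |
| 0.8 | 7.8% | 3.9% |

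**Case B: success at either time on either measure (four tests).**
- Bound: 1 − 0.95⁴ = 18.5%.
- With correlation, by simulating four normal statistics. The correlation across both time and measure is taken as the product of the two:

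| Time, measure correlation | Either direction | False claim of benefit only |
|---|---|---|
| 0.5, 0.2 | 17.1% | 8.7% |
| 0.6, 0.3 | 16.3% | 8.2% |
| 0.7, 0.4 | 15.3% | 7.6% |

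The benefit-only column is to be compared with a nominal 2.5%.

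**Case C: both times must succeed, or one overall model test decides.** The error rate is at most 5%, so there is no inflation.

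**Which case applies?** Section 10.2's simple tests run from baseline to the end of the trial, which points to 12 months but leaves out the 6-month half of the objective. The mixed model in section 10.1 could give one overall test but is only a possibility. Nothing in the protocol selects A, B or C.

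**The case against.** The strongest counter-argument is that the protocol never writes an either/or rule. The two times can be read as both being required. A mixed model could yield one treatment test, and the simple tests look only at end of trial. Testing order and alpha allocation are also often left to a SAP, which is not shown here. Part of this stands: inflation is conditional, and nothing shows that several primary tests will be run.

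A reader might go further and infer that the primary objective contains two measures, that any of four significant results is a success, and that the trial's false-positive rate therefore is 15–17%. The protocol does not support that. The objective names no instrument, DOSE and pill count appear only as collected data, and no success rule is written. The rates also depend on correlations the protocol does not give, and they count findings in either direction although the hypothesis is of improvement.

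The objection does not remove the core point. The protocol itself sets two unranked primary times and a flat 0.05 for all tests. A SAP that adjusted the level would depart from section 10.2, and one that picked a time or measure would be settling what the primary objective should already fix.

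**Conclusion.** The point holds in conditional form. The protocol does not identify one deciding comparison, and its text permits a primary claim at more than 5%.

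- If either time may count, on one measure: at most 9.75%, and about 8–9% for assumed time correlations of 0.5–0.8.
- If either measure may also count: at most 18.5%, and about 15–17% for assumed time correlations of 0.5–0.7 with measure correlations of 0.2–0.4.
- False claims of benefit: about half these rates, against 2.5%.
- If both times must succeed, or one overall test decides: no inflation.

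The second range carries the extra condition that either measure may count, so it should not be quoted without that condition. The sponsor should correct this before data are seen; it does not by itself invalidate the design.

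**What to change.** 1. In Primary Objectives and section 10.2, state that adherence at 12 months (end of the intervention and last visit) is the single primary comparison at two-sided 0.05. Test 6 months at 0.05 only if 12 months is significant. This fixed sequence holds the overall level at 5% for the named measure without splitting alpha.
2. Name one adherence measure as primary before data are seen and make the other secondary. Whether that is DOSE or pill count is the sponsor's choice, with reasons given in view of the open-label design. DOSE defines eligibility, but that alone does not make it the better outcome.
3. Tie the sample-size statement in section 10.1 to the named outcome and time.

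**Cost.** A benefit seen only at 6 months can no longer be a primary claim. Items 1 and 2 change wording only, but item 3 means justifying 376 again for the chosen outcome.

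**Alternative.** A Bonferroni split also holds 5% but costs sample size. At 90% power the multiplier is (z₁₋α/₂ + 1.282)² / (1.960 + 1.282)², which is 1.18 at 0.025 (two tests) and 1.36 at 0.0125 (four tests).

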| 1. Does not read or understand English. 2. Current use of smartphone medication adherence app(s) that include statins. 3. Concurrent use of PCSK9 Inhibitors in addition to statins and/or ezetimibe 4. Participation in another study that uses medications that could affect lipid levels 5. History of established atherosclerotic CVD, including but not limited to, atherosclerotic disease of coronary or carotid vessels or peripheral artery disease, documented ischaemic stroke (e.g., heart attack, cerebrovascular disease, peripheral artery disease) 6. Severe renal impairment defined as chronic kidney disease stage 4 and above. 7. Severe liver disease (Child-Pugh Class C) 8. Existing muscular-related complaints or diagnoses which may confound adverse event reporting 9. Uncorrected thyroid conditions, especially poorly-controlled hypothyroidism 10. Documented psychiatric diagnosis or history of mental illness or deemed as unable to give informed consent. 11. Currently pregnant, breastfeeding or expecting to get pregnant during the course of the study (1 year). 12. Guarded prognosis with expectant mortality within 12 months or less. |
| Withdrawal Criteria |
| Patients have the right to withdraw from (i.e., discontinue participation in) research at any time. They may be withdrawn from the study at the discretion of the investigator due if they fail to follow study procedure. |
| Patient Replacement |
| Patients who drop out may be replaced if the overall “lost to follow-up rate” is more than 20%. |
|  |
| **STUDY SCHEDULE** |

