| **Discontinuation Visit and Procedures** |
| In the case of patients withdrawing, or being terminated from the study due to unforeseen circumstances prior to the 1-year mark, they will be required to sign the Acknowledgment of Withdrawal form, and the CRC will have to acknowledge on the same form as well as confirmation. Patients’ decision to withdraw will not affect their medical care or any benefits to which they are entitled.  The CRC will access patient’s electronic medical record to collect clinical information (such as medications, blood test results, clinical events etc).  In cases where patient is uncontactable (“lost to follow-up”), every possible effort must be made to contact the patient and determine the reason for discontinuation or withdraws. Reasons for discontinuation or withdraws should be recorded, if possible. Clinical data collected prior to withdrawal will be retained for analysis, unless the patient disapproves it. |
| **TRIAL MATERIAL/DEVICE** N/A |
| **SAFETY MEASUREMENTS** |
| Definitions |
| **Adverse Event** – Any untoward or unfavourable medical occurrence in a patient or clinical investigation patient administered with a pharmaceutical product and which does not necessarily have a causal relationship with this treatment.  **UPIRTSO event** –refers to problems, in general, to include any incident, experience, or outcome (including adverse events) that meets **ALL** of the following criteria:   1. **Unexpected**   In terms of nature, severity or frequency of the problem as described in the study documentation (eg: Protocol, Consent documents etc).   1. **Related or possibly related to participation in the research**   Possibly related means there is a reasonable possibility that the problem may have been caused by the procedures involved in the research; and   1. **Risk of harm**   Suggests that the research places patients or others at a greater risk of harm (including physical, psychological, economic, or social harm) than was previously known or recognized.  **Serious Adverse Event** – A serious adverse event or reaction is any untoward medical occurrence which:   1. Results in or contributes to death; 2. Is life-threatening; 3. Requires inpatient hospitalisation or prolongation of existing hospitalisation; 4. Results in or contributes to persistent or significant disability or incapacity; or 5. Results in or contributes to a congenital anomaly or birth defect. |

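### Investigators may withdraw patients for not following study procedure, and nothing continues adherence measurement afterwards, so this open-label adherence trial can lose primary data unevenly and in relation to the outcome

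*Protocol*

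**What the plan says.** Four places in the protocol bear on this.

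- **Section 3.5, Withdrawal Criteria.** After the patient's own right to withdraw, it adds: "They may be withdrawn from the study at the discretion of the investigator due if they fail to follow study procedure". There is no threshold, no list of procedures, and no statement on whether outcome follow-up continues.
- **Section 3.6, Patient Replacement.** "Patients who drop out may be replaced if the overall “lost to follow-up rate” is more than 20" percent. How a replacement is allocated, and whether the replaced patient stays in the analysis, is not stated.
- **Section 6.3, Discontinuation Visit and Procedures.** For patients who withdraw or are terminated before one year, the coordinator goes to the electronic medical record for medications, blood results and clinical events. The timing is not given. It also says: "Clinical data collected prior to withdrawal will be retained for analysis, unless the patient disapproves it".
- **Section 10.2, Statistical and Analytical Plans.** "Following the principles of intention-to-treat (ITT) analysis, individuals will be retained in the group they were randomized to". The same section promises, for every visit, that "efforts will be made to minimize missing outcome data", and further on that "Sensitivity analyses will also be performed to determine the robustness of the assumption about missing data".

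The setting matters too. Section 1.2 describes the trial as open-label. The primary objective is adherence to lipid-lowering medication at 6 and 12 months. Table 1 schedules pill counts and DOSE in both arms, but app installation and coaching in the intervention arm only.

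**The concern.** Withdrawal for failing procedures is harmless to the comparison only if it is unrelated to the outcome or acts alike in both arms. Neither can be taken for granted here.

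Bringing medication to visits for a pill count is both a study procedure and a measurement of adherence. Patients enter because they are non-adherent, and those who disengage from procedures are plausibly those who also take fewer tablets. The intervention arm has two more procedures to fail, and the person using the discretion knows the arm.

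At stake is the primary comparison. If poor adherers leave the intervention arm more often than the control arm, and their 6- and 12-month DOSE and pill counts are never taken, the patients still observed in that arm look better than the arm as randomised. An analysis plan cannot recover assessments that were not made. Adding patients later restores the number but not the randomised comparison.

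**Working it through.** **1. The rules side by side.**

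| Question | What the protocol provides |
| --- | --- |
| Are withdrawn patients excluded from the analysis? | No section says so; 10.2 keeps patients in their randomised group and 6.3 keeps earlier data |
| Are LDL-C and medication records still available? | Partly: record review in 6.3, timing not stated |
| Are DOSE and pill counts continued after withdrawal? | No section says so |
| How is a replacement allocated? | Not stated |
| Does a replaced patient stay in the analysis? | Not stated in 3.6; implied by the general statement in 10.2 |

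The gap is therefore in data collection and in the wording of replacement, rather than in a stated exclusion.

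**2. The replacement trigger.** 20% of 376 is 75.2, so replacement opens once 76 patients are lost. Section 10.1 already allows for 20% drop-outs in the sample size.

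**3. Illustration of the bias.** The protocol gives no figure for this, so there is none to reproduce. Assumptions: no true effect; only completers analysed; outcome in SD units; a fraction q of an arm is withdrawn under 3.5; those patients are k SD worse than their arm's overall mean.

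The mean of those remaining improves by q·k/(1−q). The bias is the difference between arms. With SE = √(1/n₁ + 1/n₂), the two-sided rejection rate is 1 − Φ(1.96 − bias/SE) + Φ(−1.96 − bias/SE).

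Take 150 per arm (188 × 0.8 = 150.4, after the 20% allowance), then apply the withdrawals.

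*10% intervention, 0% control.* n = 135 and 150; SE = √(1/135 + 1/150) = 0.119.
- k = 0.5: 0.10 × 0.5/0.90 = 0.056 SD; bias/SE = 0.47; error rate 7.6%.
- k = 1.0: 0.10 × 1.0/0.90 = 0.111 SD; bias/SE = 0.94; error rate 15.5%.

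*10% intervention, 5% control.* n = 135 and 142.5; SE = 0.120.
- k = 0.5: 0.056 − 0.05 × 0.5/0.95 = 0.056 − 0.026 = 0.029 SD (before rounding of the terms); error rate 5.7%.
- k = 1.0: 0.111 − 0.053 = 0.058 SD; error rate 7.8%.

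*10% in both arms, same k.* Bias 0; error rate 5%.

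The first case leaves 285 of 376 analysed, so 91 (24%) are lost: the 3.5 withdrawals come on top of the 20% allowance.

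**4. A second model as a check.** Let a latent tendency to follow procedures correlate ρ with adherence, and withdraw the lowest fraction q from 188 per arm. The mean of those kept is ρ·φ(c)/(1−q), with c = Φ⁻¹(q). For q = 0.15 and 0.05, φ(c)/(1−q) is 0.274 and 0.109; with ρ = 0.3 the bias is 0.3 × (0.274 − 0.109) = 0.05 SD.

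| Withdrawn, intervention vs control | ρ = 0.3 | ρ = 0.5 |
| --- | --- | --- |
| 10% vs 10% | 0 SD, 5% | 0 SD, 5% |
| 10% vs 5% | 0.03 SD, 5.7% | 0.04 SD, 7.0% |
| 15% vs 5% | 0.05 SD, 7.5% | 0.08 SD, 12.4% |
| 20% vs 5% | 0.07 SD, 10.2% | 0.12 SD, 20.6% |

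With 5% vs 20% the sign reverses at the same size. With ρ = 0 there is no bias.

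**5. Scale.** Section 10.1 plans for an effect below 0.2 without stating the metric. If that is in SD units, a bias of 0.03 to 0.11 SD is roughly 15% to 55% of 0.2.

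**The case against.** A reader might infer that the protocol contradicts its own intention-to-treat statement. It does not. Withdrawal from the study is not exclusion from the analysis, no section removes withdrawn or replaced patients from the analysis set, earlier data are kept, and sensitivity analyses for missing data are promised. Details of the analysis set may properly sit in an analysis plan that is not shown. This stands, and it reduces the point from a contradiction to a tension that the protocol leaves open.

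A reader might also infer that the rule does remove poor adherers unevenly. That is a risk, not something the text states. The rule is permissive, covers both arms, and names study procedure rather than missed statin doses. Visits, pill counts and questionnaires apply to everyone, and no section says that ignoring the app triggers withdrawal. This stands too: equal and similarly selective withdrawal gives no bias.

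Nor is it right that only earlier data survive. The record review in 6.3 may supply some LDL-C and medication data. It does not supply DOSE or pill counts.

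On size, the upper figures assume no such withdrawal in control and a completers-only analysis. Section 10.1 mentions a possible mixed-effect model for repeated measurements, in which a patient withdrawn after month 3 or 6 still contributes. That would lessen the bias where earlier measurements predict the later ones, but not where they do not.

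On replacement, the text permits a reading in which a new patient takes the next allocation and the drop-out stays in the analysis, which is simply extended recruitment. The defect is that 3.6 does not say so.

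What survives is that withdrawal and replacement are conduct rules fixed in the protocol, and the first, followed as written, can stop primary measurements for a reason tied to the outcome.

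**Conclusion.** The point holds as a badly fixed conduct rule that should be corrected. Section 3.5 permits discretionary withdrawal, by someone who knows the arm, on a ground plausibly related to adherence and with more ways to arise in the intervention arm. No section continues DOSE or pill counts afterwards. This undermines the commitments in 10.2 to intention-to-treat and to minimising missing outcomes. Section 3.6 cannot repair the resulting attrition bias, and its silence on allocation and analysis should be closed.

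The size is illustrative. In the first model, 10% versus none gives 0.06 to 0.11 SD with an error rate of about 8% to 15%, and 10% versus 5% gives 0.03 to 0.06 SD with about 6% to 8%. The withdrawal rates, the 0.5 to 1.0 SD deficit and the completers-only analysis are assumptions. The documents do not establish that withdrawal will differ by arm, nor in which direction.

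**What to change.** **Section 3.5.** State that failing study procedures, including not using the app or coaching, does not end outcome follow-up. DOSE, pill counts and record-based LDL-C and medication data are still collected at 6 and 12 months unless the patient refuses or withdraws consent. Align the discontinuation text in 6.3 with this and give the timing of the record review.

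**Section 3.6.** State that any patient added because loss exceeds 20% takes the next allocation on the randomisation list, and that every randomised patient, including those who drop out, stays in the intention-to-treat analysis.

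**Cost.** Protocol wording and a little more follow-up contact by existing staff for a few patients. Record-based follow-up fits the present consent process, since section 11.1 already tells patients that their records may be accessed after the study. The change should be made before withdrawals occur, because missed 6- and 12-month assessments cannot be recovered.
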